## Abstract

**Background:**

In Bangladesh, most patients with Guillain-Barré syndrome (GBS) cannot afford standard treatment with intravenous immunoglobulin (IVIG) or a standard plasma exchange (PE) course, which partly explains the high rate of mortality and residual disability associated with GBS in this country. Small volume plasma exchange (SVPE) is an affordable and potentially effective alternative form of plasma exchange. SVPE is the repeated removal of small volumes of supernatant plasma over several days via sedimentation of patient whole blood. The aim of this study is to define the clinical feasibility and safety of SVPE in patients with GBS in resource poor settings.

**Methods:**

A total of 20 adult patients with GBS will be enrolled for SVPE at a single center in Bangladesh. Six daily sessions of whole blood sedimentation and plasma removal will be performed in all patients with GBS with a target to remove an overall volume of at least 8 liters (L) of plasma over a total of 8 days. Serious adverse events (SAE) are defined as the number of patients developing severe sepsis associated with the central venous catheter or deep venous thrombosis in the limb where the catheter is placed for SVPE. Based upon a predictive success rate of 75%, the SVPE procedure will be considered safe if less than 5 of 20 SVPE-treated GBS patients have a SAE. The procedure will be considered feasible if 8 L of plasma can be removed in at least 15 of 20 patients with GBS who receive SVPE. In addition, detailed clinical and neurological outcome assessments will be performed until discharge of the patient from the hospital and up to 4 weeks after study entry.

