### Indication to stop the trial

Decision to stop the SVPE trial will be designated as per a Bayesian approach [36–38]. Accordingly, a predictive success rate of 75% will be set for the SVPE procedure. If more than 5 of 20 patients experience an SAE or when it appears to be impossible to remove at least 8 L of plasma in at least 15 individual patients, the procedure will be considered unsafe or unfeasible, respectively.

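### The two published safety cut-offs do not meet: exactly 5 SAEs in 20 patients is neither safe nor unsafe

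*Protocol article*

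**What the plan says.** The protocol article states the safety decision in two places.

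- **Abstract, Methods:** "the SVPE procedure will be considered safe if less than 5 of 20 SVPE-treated GBS patients have a SAE". This awards the label safe at 0 to 4 SAEs.
- **Indication to stop the trial:** "If more than 5 of 20 patients experience an SAE", then, after the matching feasibility condition, "the procedure will be considered unsafe or unfeasible, respectively". This awards the label unsafe at 6 or more.

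Both derive the cut-off from the same benchmark. The stopping section says that "a predictive success rate of 75% will be set for the SVPE procedure", and the Abstract names the same 75%. The denominator is also the same: "A total of 20 adult patients with GBS will be enrolled for SVPE at a single center in Bangladesh".

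The feasibility criterion stands beside the safety criterion in both places. In the Abstract it reads, up to its last word, "The procedure will be considered feasible if 8 L of plasma can be removed in at least 15 of 20 patients with GBS who receive". The stopping section also uses at least 15, so feasibility passes at 15 and fails at 14 in either place.

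No other section assigns a verdict to 5 SAEs, and none describes an indeterminate zone. The Statistical analysis section covers infection rates, the standardized infection ratio and group comparisons, but gives no criterion for the primary SAE count.

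**The concern.** One benchmark, one set of 20 patients and one event type should yield one safety boundary. Here they yield two, and the count between them falls exactly on the benchmark: 5 SAEs in 20 means that 75% of patients are SAE-free.

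These cut-offs are the only stated rule for judging the primary safety outcome, since the Sample size section says that no formal power calculation was made. The Discussion makes a future randomized trial conditional on SVPE proving feasible and safe. If the count is 5, the article does not say whether that condition is met, and a reader could not tell whether the classification was fixed in advance.

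**Working it through.** **Inputs.** n = 20 and the 75% success rate (Abstract; Indication to stop the trial). Safe if X < 5 (Abstract). Unsafe if X > 5 (Indication to stop the trial). X is the number of patients with an SAE. The true SAE rate p is not in the documents, so it is assumed over 5% to 30%.

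**Step 1: the plan's own boundary.** 0.75 × 20 = 15 successes and 20 − 15 = 5 failures. The feasibility figure of 15 of 20 is reproduced, and 5 is the matching number of failures.

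**Step 2: the two safety rules side by side.**

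| SAEs in 20 | SAE-free | Abstract | Stopping section |
|---|---|---|---|
| 0–4 | 80% or more | safe | not unsafe |
| 5 | 75% | not safe | not unsafe |
| 6–20 | 70% or less | not safe | unsafe |

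The rules agree on every row but the middle one. There neither assigns a label.

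**Step 3: how likely the middle row is.** With X ~ Binomial(20, p), P(X = 5) = C(20,5) p^5 (1−p)^15, and C(20,5) = 15,504. At p = 0.25: 15,504 × 0.25^5 × 0.75^15 = 0.202. The chance of the label safe is P(X ≤ 4) if the rule is read as 4 or fewer, and P(X ≤ 5) if it is read as 5 or fewer.

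| Assumed SAE rate | P(X ≤ 4) | P(X = 5) | P(X ≤ 5) |
|---|---|---|---|
| 5% | 0.997 | 0.002 | 1.000 |
| 10% | 0.957 | 0.032 | 0.989 |
| 15% | 0.830 | 0.103 | 0.933 |
| 20% | 0.630 | 0.175 | 0.804 |
| 25% | 0.415 | 0.202 | 0.617 |
| 30% | 0.238 | 0.179 | 0.416 |

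Entries are rounded, so the columns may not add exactly in the last digit. The choice of reading hardly matters at 5% to 10%. It moves the chance of a safe verdict by about 0.20 at 25%, the failure rate that the 75% figure implies.

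**The case against.** **The two statements may serve different purposes.** One sits under a heading on stopping the trial. A success bar stricter than a stopping bar, with a borderline count between them, is a coherent design. This weakens the point but does not remove it: the stopping section itself pronounces the procedure unsafe, on the same event, patients and benchmark, and the article never says that a middle zone is intended.

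**The affected outcome may be improbable.** The SAE is narrow: severe sepsis or septic shock due to CLABSI, or thrombosis in the catheter limb. The only related rate in the article is 6.8 CLABSI per 1000 central line-days in ICUs in low-income countries (Discussion). Over 8 days that is 6.8 × 8 / 1000 = 0.054, about 5.4% per patient for CLABSI of any severity. Thrombosis and any added risk from SVPE are not quantified, so 20% to 30% cannot be excluded, but nothing in the article makes it the central case. This part stands, and it is why the range must include the low rates.

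**Safety and feasibility need not share an inequality.** Fewer than 5 fits strictly better than 75%; at least 15 fits 75% or better. A stricter bar for harm is permissible. A reader might infer from the feasibility rule that the stopping section holds the intended safety cut-off. The documents do not support that. The feasibility rule shows only that a gap-free rule was written for one endpoint and not for the other.

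**Conclusion.** The inconsistency is real and narrow. The published safety rule is not exhaustive: exactly 5 SAEs in 20 has no verdict, although that count equals the stated benchmark. The probability of landing there runs from 0.002 at an assumed SAE rate of 5% to 0.20 at 25%, assuming independent patients with a common risk. No estimate, test or sample size changes.

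Two stronger readings are tempting. A reader might infer that the two sections give opposite verdicts at 5 SAEs. They do not; each withholds its own label, and they agree at every other count. A reader might also infer that the cut-off was left open so that it could be chosen once the results were known. Nothing in the article shows this. It shows only that the text would not prevent such a choice at this one count.

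This should be fixed as an internal inconsistency. It does not undermine the study.

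**What to change.** Reconcile the Abstract and the section on stopping the trial to one exhaustive safety rule, worded the same in both places, so that 5 of 20 has a single verdict. The cut-off should come from the approved protocol (version 3 of December 2015, named under Ethical consideration) if it settles the matter, and otherwise from the sponsor and the DSMB. This review does not say which it should be.

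Rewording alone may not restore pre-specification. The Recruitment status section reports all 20 SVPE patients enrolled by June 2017, and under Data management adverse events go to the DSMB and the ERC within 24 hours, so the count may already be known. The report should therefore disclose that both wordings were published and, if exactly 5 SAEs occur, state the verdict under each.

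The cost is a check against the approved protocol, a sentence of rewording in each of the two places and a short disclosure in the report. No new data or analysis are needed.

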**Discussion:**

This is the first clinical study to evaluate the feasibility and safety of SVPE as a potential alternative low-cost treatment for the patients with GBS in resource poor settings.

**Trial registration:**

Clinicaltrials.gov NCT02780570

**Electronic supplementary material:**

The online version of this article (10.1186/s40814-017-0185-0) contains supplementary material, which is available to authorized users.

## Background

Guillain-Barré syndrome (GBS) is an acute poly-radiculo-neuropathy with a yearly incidence of 1.2 to 2.3 per 100,000 [1]. GBS is characterized by rapidly progressive symmetrical weakness of the limbs that reaches a plateau within 4 weeks. Recovery usually starts after a plateau of 2 to 4 weeks but may be delayed for months [2]. In addition, some patients experience sensory, cranial, or autonomic nerve deficits or respiratory failure. GBS is highly variable with respect to its clinical and electrophysiological presentation and differs between patients from the Eastern and Western hemisphere [3–5]. Acute inflammatory demyelinating polyneuropathy (AIDP) [3, 4] with sensory-motor involvement is the predominant form in the Western world whereas most patients in Asian countries have the acute motor axonal neuropathy (AMAN) form. At present two treatment interventions are used, that hasten the recovery of GBS. Plasma exchange (PE) was the first treatment proven to be effective in GBS, if given within 4 weeks of the onset of weakness [2, 3, 6–12]. Four sessions of standard PE (50 mL/kg plasma per session) in exchange with fresh frozen plasma (FFP) or albumin-saline mixture is beneficial in patients with GBS who are unable to walk at nadir [7, 13–16]. Efficacy of intravenous immunoglobulin (IVIG) (0.4 g/kg per day for 5 days) is similar to PE if given within 2 weeks of the onset of weakness in patients with GBS who are unable to walk [17, 18].

In low-income countries, most patients cannot afford treatment with either PE or IVIG [19]. In Bangladesh, a full course of IVIG for a 60-kg adult costs approximately 12,000–16,000 USD, and treatment with conventional PE for 5 days costs approximately 4500–5000 USD. As a result, only 15% of patients with GBS in Bangladesh are treated with IVIG or PE, while the remaining 85% of patients only receive supportive care. Patients with GBS in Bangladesh have a poor prognosis compared to patients in Western countries. We previously reported a mortality rate of 14% and observed 29% of patients with GBS in Bangladesh are unable to walk 6 months after disease onset, which may in part be due to the low rates of specific treatment with PE or IVIG [5].

Small volume plasma exchange (SVPE) may represent an effective alternative treatment for GBS. SVPE is based on the same principle as conventional PE but uses a novel but simple technique and has a much lower cost (approximately 500 USD). SVPE is achieved by repeated removal of small volumes of supernatant plasma over several days via sedimentation of patient whole blood. This study was designed to investigate the safety and feasibility of SVPE in 20 patients with GBS admitted to the National Institute of Neurosciences and Hospital in Dhaka, Bangladesh.

### Specific objectives

The objective of this study is to determine the safety and feasibility of SVPE in patients with GBS in Bangladesh.

## Methods/design

### Study design

In this safety and feasibility study, 20 adult patients with GBS will be enrolled for SVPE at the National Institute of Neurosciences and Hospital, Dhaka, Bangladesh. Patients will be monitored according to a standard protocol throughout the course of SVPE until the second day after withdrawal of the central venous catheter (CVC) to assess predefined measures of feasibility, safety, and neurological recovery. To compare the safety of SVPE in patients with GBS in the context of the background risk of central line-associated blood stream infection (CLABSI) at our institution, we will assess the incidence of CLABSI in a control group of adult patients with a diagnosis other than GBS admitted to the same intensive care (ICU) and high-dependency care (HDU) units in the same period of time (Fig. 1 and Table 1).

**Fig. 1 Fig1:**
[figure not shown]
Consolidated Standards of Reporting Trials (CONSORT) diagram for the small volume plasma exchange (SVPE) safety and feasibility study

Patient recruitment began in March 2016 and is expected to last for 18 months. Final analysis and preparation of manuscript will be done within 3 months after the last patient with GBS completes the SVPE.

### Ethical consideration

The protocol was reviewed and approved by the Institutional Review Board (IRB) consisted with Research Review Committee (RRC) and the Ethical Review Committee (ERC) at icddr,b (Protocol Number: PR-15086, Version no. 3, Date: December 9, 2015). The study will be performed according to the Declaration of Helsinki [20]. Only patients who provide informed signed consent to the study physician would be included in the study. The participants will be informed that participation in the trial is voluntary and that they can withdraw consent at any time without giving reasons. Expenditure for the patients with GBS treated with SVPE and any harm related to the SVPE will be fully compensated.

### Patient enrolment—case definition

#### Patients with GBS

Patients ≥ 18-years of age fulfilling the diagnostic criteria for GBS of the National Institute of Neurological and Communicative Disorders and Stroke (NINDS) [21] will be enrolled, provided they are unable to walk unaided for more than 10 meters (GBS disability score ≥ 3), presented within 2 weeks of the onset of weakness, and are unable to afford standard treatment with IVIG or PE. Patients with severe or terminal concomitant illness, evidence of healthcare-associated infection on admission (except for aspiration pneumonia), or a previous history of severe allergic reaction to properly matched blood products and pregnant women will be excluded from the study.

#### Patients without GBS

Patients ≥ 18-years of age with a diagnosis other than GBS requiring a CVC for > 2 to ≤ 8 calendar days after admission to the same ICU and HDU units in the same period of time will be eligible. Patients with healthcare-associated infection present on admission (except aspiration pneumonia) and pregnant women will be excluded from the control group.

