### Attempts to minimize the risks associated with SVPE

All connection ports of the SVPE kit (Fig. 2), the lumens of the CVC, the blood bag, and the saline bag will be disinfected with 70% alcohol and then air-dried before sampling blood or disconnection. Strict aseptic procedures will be followed to prevent CLABSI [25–27]. The SVPE procedure will not be started or stopped temporarily after the start of SVPE in patients who develop hypotension (30 mmHg decrease in systolic blood pressure, systolic blood pressure < 90, or MAP < 65 mmHg) or cardiac arrhythmia for any reason. After correction of hypotension and/or cardiac arrhythmia, the SVPE procedure will be started or restarted if SVPE stopped due to autonomic instability. The CVC will be removed as soon as SVPE is completed or the CVC will be immediately relocated to another insertion site if a CLABSI related to the CVC used for SVPE is confirmed or strongly suspected. Patients with GBS having severe sepsis as per standardized definition (Additional file 1: Appendix 1A) due to any organ site-specific infection present on admission (except for aspiration pneumonia) will be excluded for SVPE. Otherwise, any covert infection or aspiration pneumonia, as may be indicated by leukocytosis, will be investigated and treated accordingly after consultation with a medical microbiologist. Normal hemoglobin concentration for > 18 years man and non-pregnant woman will be considered as 13 and 12 g/dL, respectively [28]. However, blood transfusion will be considered to correct severe anemia (hemoglobin level < 8 g/dL [28]) before, during, or after SVPE. Proper screening of FFP for specific infective agents (hepatitis B and C viruses, human immunodeficiency virus (HIV), and syphilis) will be performed prior to administration of FFP.

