### Sample size

This safety and feasibility study will enroll 20 patients with GBS for SVPE. We cannot perform a formal power calculation for this safety and feasibility study. The sample size is based on previous pilot studies in GBS [34, 35]. The baseline rate of CLABSI will be measured in parallel in patients without GBS (and not undergoing SVPE) admitted to the same study facility who require a CVC during the study period. All control patients available during the inclusion time period will be included. We expect to obtain at least 20 or more (i.e., the maximum number of patients possible during the study period) control patients without GBS who require a CVC for at least 2 days and maximum of 8 days.

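### Controls qualify only if their catheter ends up lasting no more than 8 days, and two illness exclusions for GBS patients are not applied to them, so the secondary CLABSI comparison is not like-for-like

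*Protocol article*

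**What the plan says.** Under Patients without GBS, the catheter window for controls is an eligibility criterion: they are patients "with a diagnosis other than GBS requiring a CVC for > 2 to ≤ 8 calendar days after admission". Sample size repeats it as a property of the patients to be recruited: "who require a CVC for at least 2 days and maximum of 8 days". The upper limit agrees in the two places. The lower limit does not: one section requires more than 2 days, the other accepts exactly 2.

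The control exclusions are short: "Patients with healthcare-associated infection present on admission (except aspiration pneumonia) and pregnant women will be excluded from the control group". GBS patients are screened more strictly. Patients with GBS excludes "Patients with severe or terminal concomitant illness, evidence of healthcare-associated infection on admission" and further categories. Attempts to minimize the risks associated with SVPE adds: "Patients with GBS having severe sepsis as per standardized definition", where the sepsis is "due to any organ site-specific infection present on admission (except for aspiration pneumonia) will be excluded for SVPE". Neither the co-existing-illness exclusion nor the sepsis exclusion is listed for controls.

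The controls have two uses. Secondary outcome measures names a relative risk of CLABSI against them. Statistical analysis takes the predicted number of infections in the standardized infection ratio (SIR) from their rate. The primary safety rule (Abstract; Indication to stop the trial) is a count of SAEs among the 20 SVPE patients and uses no control data.

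**The concern.** Completed catheter duration is information from after entry, and infection can alter it. Take a patient whose catheter was meant to stay two weeks. If it becomes infected on day 6 and is taken out, the patient qualifies as a control and brings an event. If it stays clean past day 8, the patient is ineligible and the event-free days up to day 8 are lost. Nothing in the GBS criteria selects on duration in this way.

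The unmatched exclusions are a second difference. Controls may include patients with severe co-existing illness or severe sepsis at admission, who could plausibly have a different infection risk.

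The Discussion calls catheter infection the major safety concern and says that no Bangladeshi ICU or HDU data on CLABSI exist. No local published rate is therefore available to show that the reference is distorted. A wrong control rate passes directly into the SIR, and a follow-on randomized trial is planned if the procedure proves feasible and safe.

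**Working it through.** The article gives no expected control rate, power or formula on this point, so there is no figure to reproduce. The check asks what the ≤ 8-day condition does when the true infection hazard is equal in both groups.

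**Inputs**
- From the document (Discussion): 6.8 CLABSI per 1000 central line-days, used as a daily hazard h = 0.0068.
- From the document: controls must have catheters lasting more than 2 and at most 8 days; 24 controls and 20 SVPE patients were recruited (Recruitment status).
- Assumed: infection and line-days count from day 3 until infection or removal; planned stays are uniform on 3–8 days (short) or 9–21 days (long); a share p of candidates is long-stay; a share r of CLABSIs ends the catheter that day.

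**Building blocks**
- Short stay: days at risk, mean of [1 − (1 − h)^n]/h over n = 1 to 6, is 3.461. Events per patient: 0.0068 × 3.461 = 0.0235.
- Long stay: chance of CLABSI on days 3–8 is 1 − (1 − 0.0068)^6 = 0.0401. Mean at-risk days among those infected: 3.48.
- Under the eligibility rule, a long-stay patient enters only if infected and removed by day 8.

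**Observed control rate** = [(1 − p) × 0.0235 + p × r × 0.0401] / [(1 − p) × 3.461 + p × r × 0.0401 × 3.48]

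For p = 0.25, r = 1: 0.02768 / 2.630 = 10.5 per 1000. With no true difference, the ratio reads 6.8 / 10.5 = 0.65.

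| Long stays | r = 1: rate, ratio | r = 0.5: rate, ratio | r = 0: rate, ratio |
|---|---|---|---|
| 10% | 8.0, 0.84 | 7.4, 0.92 | 6.8, 1.00 |
| 25% | 10.5, 0.65 | 8.7, 0.78 | 6.8, 1.00 |
| 50% | 17.7, 0.38 | 12.4, 0.55 | 6.8, 1.00 |

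Including every catheter beyond 2 days and censoring at day 8 gives 6.8 per 1000 in every cell. Simulation of the same model agrees.

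**Can it reverse?** A second simulation used a hazard of 6.8 or 20 per 1000 from day 3, elective removal of 0.1 to 0.3 per day, all device-days counted, and optionally half the patients sicker, with 2 to 3 times the infection hazard and longer stays. The control rate under the rule, divided by the rate with censoring at day 8, was:
- 1.2 to 3.5 if CLABSI always ends the catheter;
- 1.1 to 2.2 if it does so half the time;
- 0.67 to 0.95 if it never does, so that an SIR with no true difference reads about 1.05 (1/0.95) to 1.5 (1/0.67).

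The reversal arises because short stays consist more of early days on which no infection can be counted and because, when sicker patients keep catheters longer, the rule drops them.

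**Per-patient relative risk.** With the same daily hazard on every catheter day, the risk over 8 days is 1 − 0.9932^8 = 5.3%. Over an assumed 5 days it is 3.4%, and over 3 days 2.0%. The relative risk is then about 1.6 (8 v 5 days) or 2.6 (8 v 3 days) with no true difference, against SVPE.

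**The case against.** A reader might infer that the rule inflates the reference rate and so makes SVPE look safer. The documents do not support that as a firm statement. Inflation needs CLABSI to end a control's catheter. The only instruction on this concerns the SVPE catheter, and it describes relocation to another site. Nothing is said about control catheters. Without removal the bias disappears or may reverse, and on a per-patient scale shorter control exposure pushes the relative risk the other way. All of this stands.

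The counts are small, which also stands. At 6.8 per 1000, about 1.1 CLABSI are expected in 20 × 8 = 160 SVPE device-days and 0.8 in 24 × 5 = 120 control days (5 days assumed). With full removal, the expected number of infected long-stay patients among 24 controls is 24 × 0.0401p / [(1 − p) + 0.0401p], or 0.1, 0.3 and 0.9 at 10%, 25% and 50% long stays. Sampling error will be large beside this in all but the extreme case.

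The illness criterion does not transfer directly. For a GBS patient it means illness alongside GBS; for an ICU or HDU control, severe illness may be the reason for admission. Because controls with healthcare-associated infection on admission are already excluded, the sepsis gap is mainly community-onset disease. This argues against simply copying the exclusions, but not against showing their effect.

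Finally, the 8-day limit might be read as an observation window. The Sample size wording, which describes the patients to be obtained, favours eligibility.

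**Conclusion.** The point holds for comparability, not for a fixed direction. Control eligibility conditions on a post-entry duration that infection can change, GBS eligibility does not, and two GBS exclusions have no control counterpart. The SIR and the relative risk of CLABSI are therefore not like-for-like.

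On the device-day scale, the SIR is biased in favour of SVPE if CLABSI prompts removal: a true ratio of 1 reads 0.84 to 0.38 with full removal and 0.92 to 0.55 with half, at 10 to 50% long stays. These figures are illustrative. Only the 6.8 per 1000 comes from the article; the stay distributions, long-stay shares and removal shares are assumed. The effect of the unmatched illness exclusions cannot be sized from the article.

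It would go too far to conclude that the trial's safety decision is compromised. That decision rests on an absolute SAE count in the SVPE patients, and the control comparison is secondary and unpowered. The disagreement over the lower limit is real but minor.

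**What to change.** - Include every otherwise eligible non-GBS patient whose catheter is in place more than 2 calendar days, whatever its later duration.
- Censor line-days and CLABSI at day 8, counting from the same catheter day in both groups.
- Make the CLABSI comparison per device-day rather than per patient.
- State the lower limit as more than 2 calendar days in both Patients without GBS and Sample size.
- Show the control rate with and without patients who would have met the GBS illness or sepsis exclusions, rather than imposing those exclusions outright.

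The cost is revised eligibility and analysis wording plus some record review for long-stay patients. The article does not say whether they were under surveillance, and recruitment is reported as complete. If they cannot be recovered, report the selection as a limitation of the SIR and say that its direction depends on whether infected control catheters were removed.
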